### Study Participants

The study aims to recruit a total of 260 pregnant Emirati females during their first trimester (8–12 weeks of gestation) through face-to-face recruitment at OB-GYN clinics in selected health care facilities across the Emirates of the UAE. The participants will be provided with both verbal and written information (Participant Information sheet) about the study aims, data collection activities, and duration of the study. Mothers will consent to the study on behalf of their children to be included in the study, by signing a form, after meeting the following inclusion and exclusion criteria.

Inclusion Criteria:

•Emirati Nationality•Within first trimester of pregnancy (between 8–12 weeks of gestation)•Singleton pregnancy•Absence of major illness preconception (Diabetes mellitus, hypertension, kidney disease, cancer, epilepsy, severe psychiatric illness, and other chronic diseases of infections such as autoimmune disorders, human immunodeficiency virus, and hepatitis).

Exclusion Criteria:

•Non-Emirati Nationality•Unconfirmed viable, intrauterine pregnancy at first obstetric ultrasound during first trimester•Twin or multiple gestation pregnancy and a history of multiple gestations•History of chronic illness (i.e., T2DM, hypertension, etc.)•Previously given birth to babies with malformation, intellectual disability, or inborn errors of metabolism.•Experience of a miscarriage before 28 weeks of gestation•Use of significant regular medications, including insulin, anti-hypertensive agents, psychotropic medications, anti-epileptic drugs, steroids, immune-suppressive agents, and chemotherapeutic agents.

### Study Protocol

The study protocol is summarized in Figure 1. Each mother/child will be assessed over 3 years, at 11 separate study visits.

**FIGURE 1 F1:**
[figure not shown]
Assessment timeline for the UAE Birth Cohort Study (UAE-BCS).

#### During Pregnancy

Pregnant females will be recruited during their first trimester (8–12 weeks of gestation) in OB-GYN clinics and perinatal health facilities in the UAE. There will be one visit during each trimester of pregnancy, and an additional eight visits postpartum. The initial prenatal assessment screening will aim to measure key factors such as diet and supplement use, physical activity and lifestyle practices, maternal psychological, sociodemographic, and socioeconomic characteristics, through anthropometric measurements and validated questionnaires. Blood samples will be collected from participants during the first and third trimester for biochemical analysis of several biomarkers. Maternal exposure, knowledge, attitudes, and intention toward infant feeding practices will be assessed during the third trimester through questionnaires. Information on fetal growth from ultrasound will be collected during the second and third trimester.

#### Post-partum

The participants’ hospital records will be used to obtain information about the delivery, as well as birth outcomes data. Postnatal visits will take place when the child is 0.5, 4, 6, 9, 12, 18, and 24 months old. These visits will consist of anthropometric measurements and assessment of child feeding practices (breastfeeding and complementary feeding practices, dietary intake, supplement use, and the eating environment at home). Developmental assessments will take place at three points: (a) within 2 weeks of birth, (b) at 10–14 months, and (c) at 22–26 months of age. In addition, the mothers will undergo postpartum assessment at each postnatal visit. This will consist of anthropometric measurements, collection of dietary intake data, supplement use, lifestyle habits, physical activity, and psychological state.

#### Data Collection Instruments and Methods

Culture specific and English and Arabic questionnaires were developed for the purpose of data collection for this study. In addition, questionnaires for infant neurological development and neonatal forms were provided by an expert in the field and translated into Arabic. The content and validity of all questionnaires was confirmed by experts in each respective field. A pilot study was conducted to test the wording, cultural appropriateness of the questionnaires, and to ensure they would yield the required data. The questionnaires will be administered by trained research nutritionists through face-to-face interviews.

### Sociodemographic and Lifestyle Questionnaires

This questionnaire will be used to collect sociodemographic information about the parents, including age, education, employment status, income, dietary, and lifestyle influences and choices, and household details including information about living arrangements, such as type of accommodation. Additional paternal information collected in this questionnaire include brief questions about general health.

#### Maternal Dietary Intake Assessment Questionnaire

Maternal dietary intake information will be collected through Food Frequency Questionnaires (FFQ) and multiple pass 24 h food recalls and will be used to assess energy, nutrient intake, and dietary patterns. The FFQs contain 130 culture-specific food items, and supplement use will also be collected during the 24-h recall. The FFQs were specifically created for population studies in the UAE and will include foods traditionally consumed during pregnancy. Additionally, the FFQs will contain questions about the weekly consumption frequency of different foods and food groups. The United States Department of Agriculture Multiple Pass Food Recall (MPFR), which is a 24-h recall method used to collect detailed dietary intakes and supplement use of participants to allow capture of all food and beverage consumption during the 24 h preceding the interview, and is validated for accurate measurement of food intake (35). The 24-h food recalls will be analyzed with the ESHA Food Processor, SQL (ESHA Research, V. 11. 0) to calculate energy and nutrient intake in the participants (36). During the study, both the FFQs and the 24-h recalls will be conducted during the first, second and third trimester, and 4 months post-partum.

#### Physical Activity Questionnaire

A pregnancy-specific physical activity questionnaire used in a similar study in Qatar and Lebanon will be used to assess the physical activity levels of the participants during their second trimester (37). The International Physical Activity Questionnaire (IPAQ) will be used to collect physical activity levels of the mother at each child follow up visit (38).

#### Infant and Young Child Feeding Practices and Dietary Intake

The WHO indicators will be used as benchmarks to assess child breastfeeding and complementary feeding practices and will include questions related to breastfeeding and complementary feeding (39). A 24-h recall using the mother as a proxy for the child’s dietary intake and supplement use will be used for evaluation at each of the visits post-partum.

### Anthropometric Assessments

Anthropometric measurements of the mothers, infants and young children will be obtained at different stages throughout the study.

#### Anthropometric Assessment of Mothers

Maternal anthropometric measurements will be taken during pregnancy and will follow standard techniques for obtaining height in centimeters (cm) using a stadiometer during the first trimester, weight in kilograms (kg) using Tanita scale (Tanita BC-418, Tanita Corp., Tokyo, Japan) at all visits, waist circumference in centimeters using a non-stretchable measuring tape during the first trimester and percentage body fat which will be assessed by bioelectrical impedance analyzer (Tanita BC-418, Tanita Corp., Tokyo, Japan) during the first trimester and during all postnatal visits.

#### Anthropometric Assessment of Infants and Young Children

Anthropometric assessment of infants and young children will be taken at each of the six visits after birth and will include measurement of weight, length, head circumference and mid-upper arm circumference (MUAC). Anthropometric measurement protocols and quality control procedures will follow the WHO MGRS INTERGROWTH-21st Project protocol (40–42). Study equipment will include portable electronic weighing scales (Seca model 376; Seca, Hangzhou, China); recumbent length will be measured using a Harpenden Infantometer (range 300–1,100 mm; Chasmors Ltd., London, United Kingdom), flat metal tape measure will be used for head circumference measurement (CMS ref.3105; Chasmors Ltd., London, United Kingdom). MUAC will be measured using a tape around the arm at the level of the midpoint (42).

#### Early Child Development Assessments

For this study, a set of formal validated questionnaires and developmental assessment tools will be used to assess the child’s growth milestones and development, such as vision, hearing, attainment of certain reflexes and motors kills, social-emotional behaviors, and language.

Assessment of early child development (ECD) will occur at three timepoints: (i) within 2 weeks of birth; (ii) at 10–14 months of age; and at 22–26 months.

The first developmental assessment will take place within 2 weeks and consist of a brief examination of the newborn for color, posture, tone, reflexes, suck, behavior and dysmorphic features using a novel tool, the Neonatal Neurodevelopment Assessment (Neo-NDA). In a sub-sample of 30 participants, the Dubowitz’s neurological examination (43), a clinical examination of neonatal tone, reflexes and behavior will be administered together with the Neo-NDA.

The second developmental assessment will occur at 10–14 months of age, using the Oxford Neurodevelopment Assessment (OX-NDA). The OX-NDA is a 57-item measure and assesses nine domains: cognition (15 items); fine and gross motor (8 items); language (8 items); behavior (7 items); executive function (3 items); attention (5 items); social-emotion reactivity (9 items); and positive affect (2 items). The instrument has a combination of directly administered, concomitantly observed, and maternally reported items. The child’s performance on each item is reported on a five-point scale. The OX-NDA was designed to be an international, population-based screening measure for assessing early child neurodevelopment without the need for specialist professionals or infrastructure and has been validated against the Bayley Scales of Infant Development in a sample of 522 from Pelotas, Brazil (44). Hearing will be assessed by mapping 11 items on the OX-NDA onto 4 auditory milestones for the 10–14 months age group (45). Vision outcomes in the infants will be evaluated using the Cardiff Tests, which measure visual acuity and contrast sensitivity (46, 47). Mothers will report on the sleep of their infants using a modification of the brief infant sleep questionnaire (48).

The final developmental assessment will occur at 22–26 months of age, using the INTERGROWTH-21st Neurodevelopment Assessment (INTER-NDA) (49, 50). The INTER-NDA is a 53-item assessment of cognition, expressive and receptive language, gross and fine motor skills, behavior, attention, and social-emotional reactivity in children 2 years old. Outcomes are reported on a 5-point scale characterizing the child’s performance in each domain across a spectrum. Like the OX-NDA, it designed to be free from cultural biases and is based upon objective reporting (rather than subjective judgment) of the child’s performance. It consists of directly administered, concurrently observed, and caregiver reported items. It’s inter-rater and test-retest reliability are *k* = 0.70, 95% CI: 0.47–0.88 and *k* = 0.79, 95% CI: 0.48–0.96, respectively (49), and the INTER-NDA shows good agreement with the Bayley Scales of Infant Development III edition (intraclass correlations for domains ranging between 0.745 and 0.883; *p* < 0.001). The INTER-NDA has been used to assess ECD outcomes in over 5,000 children from 12 countries.^1^ Hearing will be assessed by mapping 6 items on the INTER-NDA onto 3 auditory milestones for the 22–26 months age group (45). Vision outcomes in the infants will be assessed using the Cardiff Tests, and mothers will report on infant sleep outcomes on a modification of the brief infant sleep questionnaire.

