The first 1,000 days of life are a vital period that play a crucial role in the development of the immune, endocrine, metabolic, motor, and other developmental pathways. Maternal nutrition and lifestyle choices in preconception and during pregnancy have significant influences on the health, growth, and development of the fetus. Research shows that a maternal diet low in protein is connected to changes in the structure of the liver of the fetus and low birth weight (14), while a diet rich in fat effects adipocyte metabolism, fetal growth, and fat mass in the offspring (15, 16). Maternal anemia and iron, folate, or vitamin B12 deficiency during pregnancy is associated with an increased risk of fetal growth restriction, premature birth, and low birth weight (17–19). The effect of maternal nutrition on the cognitive capability and neurodevelopment of offspring is well established, particularly in the context of micronutrient deficiencies. Vitamin B12 deficiency is associated with spina bifida and infant insulin resistance (20), and maternal iodine deficiency with hypothyroidism. Prenatal maternal iron deficiency is associated with decreased myelination, disturbance in monoamine neurotransmitter synthesis and hippocampal energy metabolism in offspring (21), and there is evidence of an association between increased consumption of essential long-chain omega -3 fatty acids during pregnancy and better infant performance in development assessments, verifying the link between prenatal and postnatal diet to specific aspects of the brain development (22). The effect of prenatal maternal nutrition on neurodevelopment outcomes in children is not exerted solely through the effect of maternal nutrition on fetal growth and birth outcomes. It persists into the postnatal period, by impacting the quality and quantity of breast milk, maternal mood, and infant feeding practices.

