Frequencies and percentages will be used to describe categorical variables and mean, and standard deviations will be used to describe continuous variables. The chi-square test (χ2) or Fisher’ s exact test will be used to calculate the association between categorical variables. Independent *t*-tests and Mann-Whitney tests will be used to chart comparisons for normal and non-normal continuous variables, with normality of variables evaluated using the Kolmogorov-Smirnov and Shapiro-Wilk tests. Associations among the variables of the cohort study (i.e., maternal factors, birth outcomes, breastfeeding, complementary feeding, growth patterns, etc.) will be examined using simple linear and logistic regressions. The two main dependent variables in this study are related to birth outcomes and growth patterns of the child. Variables showing statistical significance in the univariate analysis will be included in the multivariate models as covariate factors in order to control for potentially confounding variables that have been used in the model. Parameter estimates and their respective 95% confidence intervals will be calculated for linear regression analyses, whilst for logistic regression analyses odds ratios and their respective 95% confidence intervals will be calculated. Tests for linearity (tolerance > 0.4) of the covariates included in the regression models will be performed. Normality of the residuals will be assessed using the histogram of standardized residuals and normal probability plot in all linear regression models. *P*-values less than 0.05 will be considered to indicate statistical significance.

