The overall prevalence of global developmental delay and pervasive developmental disorder among 3-year-old children in the UAE in 2016 was reported to be 2.44% and 29/10,000 for severe delay/disorder with a prevalence of 8.4% and 58/10,000 for mild to moderate delay/disorder, respectively, with no reports profiling the neurodevelopment abilities of young children during the first 1,000 days of life from UAE (28). Therefore, the importance of the first few years of a child’s life to decreasing the risk of disease morbidity, mortality, and later risk of chronic disease, and to promoting healthy growth and development, is important. Moreover, nutrition during the first 1,000 days of a child’s life has been identified as one of the significant modifiable factors, during this critical window of opportunity, to influence optimal growth, promote optimal neurodevelopment and reduce disease vulnerability later in life (61). In addition, the data obtained in this study will support the development and validation of a new tool, the Neo-NDA, to be used for the measurement of neurological status and maturity of new-borns in the UAE; explore the association between early childhood development (ECD) outcomes using the three inter-related tools: Neo-NDA, the OX-NDA and the INTER-NDA at < 5, 12, and 24 months of life; and use holistic and standardized measures of ECD, importantly including measure of vision, hearing and sleep at all developmental assessments. Prenatal maternal nutrition is an important predictor of fetal and child brain development, exerting its effect in both intrauterine (fetal growth and birth outcomes) and extrauterine (parenting, child feeding practices, maternal mood, quality, and quantity of breast milk) environments. There is limited understanding on what constitutes optimal ECD, with most studies employing heterogeneous methodologies for ECD assessment and being carried out in high-income western settings. This has limited both the comparability and generalizability of neurodevelopmental evaluations, between studies, and to other populations. It also restricts their scalability for measuring and monitoring ECD at a population level with routine ECD screening programs lacking in many parts of the world. To our knowledge, there are no studies profiling neurodevelopmental outcomes during the first 1,000 days of life in the UAE, and therefore our findings will fill this gap. There is a need for high quality data to be collected in country/geography-specific large birth cohorts, using standardized methodologies, to guide understanding of what constitutes optimal and sub-optimal child development in these contexts, to permit comparability between populations, representing a scalable solution to the application of ECD surveillance in these settings. Birth cohort studies that commence either during pregnancy or preconceptionally and then follow the offspring and the wider family into later life, can make a significant contribution to the development of dietary recommendations to expectant mothers during pregnancy to maximize the health and development of the offspring while simultaneously contributing to the understanding of optimal and sub-optimal ECD outcomes in the context of maternal nutrition. Maternal and infant nutrition, as well as early child growth, health, and development, should be a priority for health policy implementation, health promotion activities, and interventions.

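### Adjustment for exact age at the OX-NDA and INTER-NDA is left to a significance screen and no correction for gestational age is stated, so lower maturity at testing can pass for poorer development

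*Protocol article*

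**What the plan says.** Under Early Child Development Assessments, the protocol article sets three time points: "i) within 2 weeks of birth; (ii) at 10–14 months of age; and at 22–26 months". It then assigns the instruments: "The second developmental assessment will occur at 10–14 months of age, using the Oxford Neurodevelopment Assessment (OX-NDA" and "The final developmental assessment will occur at 22–26 months of age, using the INTERGROWTH-21st Neurodevelopment Assessment (INTER-NDA".

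Scoring is described as performance on five-point scales. For the INTER-NDA: "Outcomes are reported on a 5-point scale characterizing the child’s performance in each domain across a spectrum". Hearing at the second assessment uses one milestone set for the whole band: "mapping 11 items on the OX-NDA onto 4 auditory milestones for the 10–14 months age group". The article mentions neither corrected age nor age-standardised scores.

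The covariate rule, under Statistical Analysis and Sample Size Calculation, is explicit: "Variables showing statistical significance in the univariate analysis will be included in the multivariate models as covariate factors".

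Four other places bear on the point:

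- The Introduction describes maternal anemia and iron, folate or vitamin B12 deficiency as "associated with an increased risk of fetal growth restriction, premature birth, and low birth weight". Objectives lists hemoglobin, ferritin, folate and vitamin B12 among the exposures.
- Objectives names preterm birth among the factors to be studied, and Study Participants does not exclude it.
- The sample size paragraph adds 10% for losses that include preterm delivery.
- Delivery and Birth Outcome Data shows that gestational age and date of delivery are collected.

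**The concern.** Two mechanisms are at work and they should be kept apart.

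The first has a direction. Of two children tested at the same age since birth, the one born earlier has had less time to develop since conception and can be expected to score lower for that reason alone. The protocol itself ties some of the exposures to early birth. If ages are not corrected, part of any association between maternal micronutrient status and the developmental score may reflect maturity on the day of the test.

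The second is noise. A four-month band is one third of a child's age at 12 months. If test age is unrelated to exposure, its spread does not bias the association; it inflates the score variance and weakens the observed correlation.

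An ordinary age term would deal with the second mechanism, but the stated rule makes that term depend on a significance test. Age at testing varies because the visit band lets it vary, so whether it is in the model should not turn on a p-value. Even if age since birth passes the screen, it does not remove the gestational part.

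**Working it through.** **The plan's own figure.** Fisher z, two-sided 5%, 80% power, r = 0.20:

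n = ((1.960 + 0.842) / atanh(0.20))² + 3 = (2.802 / 0.2027)² + 3 = 193.97, so 194, as stated. Then 194 × 1.35 = 261.9, against 260 stated, which is close enough. Neither figure involves developmental age.

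**Inputs.** From the article: the two bands (10–14 and 22–26 months), r = 0.20 and n = 194. Assumed, because the documents give no value: a score gain b of 0.05 to 0.3 SD per month of age, test age spread evenly over the band, and 40 weeks as the reference for term (4.345 weeks per month).

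**Immaturity from early birth.** Shortfall in months = (40 − weeks at birth) / 4.345; score deficit = b × shortfall.

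| Born at | Shortfall (months) | Deficit, b = 0.05 to 0.3 (SD) |
|---|---|---|
| 36 weeks | 4 / 4.345 = 0.92 | 0.05 to 0.28 |
| 34 weeks | 6 / 4.345 = 1.38 | 0.07 to 0.41 |
| 32 weeks | 8 / 4.345 = 1.84 | 0.09 to 0.55 |

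A child born at 34 weeks and seen at 10 months since birth is 10 − 1.38 = 8.6 months by corrected age, below the band to which the hearing milestones are tied.

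**Noise from the width of the band.** An even spread over 4 months has SD 4/√12 = 1.155 months. Variance added to a unit-variance score is v = (1.155 b)². The observed correlation is 0.20/√(1 + v), and power at n = 194 follows from Fisher z. The last column is the chance that age, with true correlation √(v/(1 + v)), reaches p < 0.05 univariately at n = 194.

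| b (SD/month) | Share of variance due to age | Observed r | Power | Chance age passes the screen |
|---|---|---|---|---|
| 0.05 | 0.3% | 0.200 | 79.9% | 13% |
| 0.10 | 1.3% | 0.199 | 79.5% | 36% |
| 0.20 | 5.1% | 0.195 | 77.9% | 89% |
| 0.30 | 10.7% | 0.189 | 75.3% | over 99% |

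The observed r and power assume age is left out of the model. Where the loss is largest, the screen would nearly always admit age if it is tested as a candidate; where age is likely to be missed, the loss is trivial. The noise is therefore the minor part of this point. The deficits in the first table remain whichever way the screen falls, unless age is corrected for gestation.

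**The case against.** The strongest reply is that the article is silent, not wrong. It never says that the 10–14 and 22–26 month ages are uncorrected, and a condensed article commonly leaves scoring and prematurity rules to a fuller document or the instrument manual. That stands: a reader might infer that the plan commits to uncorrected age, and the text does not support that. What is not silent is the covariate rule, which as written does not secure an age term.

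Four further objections limit the point.

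- **Size of the power loss.** A reader might infer a serious loss. Taking a developmental SD of 15% of age gives 1.8 months at 12 months, or 0.56 SD per month, and power of 65%. Nothing in the documents supports that slope. With it, age would explain 29% of the variance and would almost surely pass the screen. An even spread is also near the worst case, since Post-partum sets visits at 12 and 24 months.
- **Preterm losses.** The sample size paragraph counts preterm deliveries as losses. If those children leave the analysis, most of the prematurity effect goes with them. Not all of it does: births at 37 and 42 weeks still differ by 5 / 4.345 = 1.15 months. The text does not settle whether they leave, given that Objectives studies preterm birth.
- **Status of the outcome.** Development is not one of the two main dependent variables, which concern birth outcomes and growth.
- **The newborn examination.** Its window is two weeks, not four months, and maturity is part of what the Neo-NDA is meant to measure. The Discussion places the tools at different times, "Neo-NDA, the OX-NDA and the INTER-NDA at < 5, 12, and 24 months of life", but the first of these looks clerical (Post-partum uses 0.5 months) and says nothing about age correction.

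**Conclusion.** The point holds in a limited form. For the OX-NDA and INTER-NDA, the article states four-month bands, describes no age standardisation or correction for gestation, and leaves exact test age to a univariate screen. Because the protocol links several exposures to premature birth, immaturity at testing can enter the nutrition–development association with a consistent direction.

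The size depends on an assumed gain of 0.05 to 0.3 SD per month: 0.07 to 0.41 SD for a child born at 34 weeks, and a correlation of 0.20 observed as 0.189 to 0.200, with power 75% to 80% at n = 194. How much bias reaches the cohort-level association cannot be computed, because the documents give neither the strength of the link between exposure and gestational length nor the number of preterm children analysed. The sample size of 194, raised to 260, stands. This is an inexpensive improvement to the analysis of an outcome outside the two main ones, not a flaw in the study's primary basis.

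**What to change.** In Statistical Analysis and Sample Size Calculation, add a rule for developmental outcomes:

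- Exact age at testing enters every OX-NDA and INTER-NDA model as a fixed covariate, outside the univariate screen.
- For preterm children this is corrected age; alternatively, use age-standardised scores. State in Early Child Development Assessments whether the age bands are chronological or corrected.
- Gestational age as a covariate in its own right is kept for a separate, declared analysis. The Introduction and Discussion treat birth outcomes as one route from maternal nutrition to development, so adjusting for it in every model could remove part of the effect under study.
- Reconcile Objectives with the sample size paragraph: say whether preterm children are followed and analysed or counted as losses.

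The cost is a few sentences. Gestational age and delivery date are already collected, and the visit date gives exact age. One extra model term is negligible at this sample size.
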